**Fig. 1 Fig1:**
[figure not shown]
Flow chart of the research process

All participants will receive a telephone call from one of the researchers to help them access the web page. All participants will also be able to call for support in the use of the website. If needed, the researcher will provide instructions for navigating the website to help the participants to access the videos, text, and the peer-support communication forum. Being familiar with the content of each text and video, the researcher can guide family caregivers to specific content when a specific issue is raised.

### Outcomes

The study focuses on preparedness for caregiving and preparedness for death as these concepts have earlier been shown to be clearly and closely related to each other in the context of palliative cancer care. The secondary outcomes are: changes in family caregivers’ knowledge about medical issues, their communication with the patient, and their considerations of the future. These concepts are related to the topics that the intervention addresses. Other secondary outcomes will be the physical and psychological health and quality of life for the family caregiver 1 year after the patient’s death. Outcomes will also relate to the feasibility of the website’s framework, content, uses and family caregivers’ experiences of using the website.

Information about which participants have logged on to narstaende.se, which videos have been watched and how many times a specific video was watched can be gathered electronically. Information on how long the participant stays on certain pages can also be obtained. These factors can thus be studied in relation to preparedness for caregiving as well as preparedness for death.

### Data collection and measures

Data will be collected with the use of qualitative interviews and a study-specific questionnaire that has been developed based on earlier studies and in face-to-face validation [43–45]. The questionnaire includes:
background variables such as age, gender, and education,the Preparedness for Caregiving Scale, which measures perceived readiness for various domains of caregiving [5]. It has been translated into Swedish and has demonstrated good validity and reliability for caregivers in palliative care [43, 46]. It consists of eight items answered on a 5-point Likert-type response scale, ranging from ‘not at all prepared’ (0) to ‘very well prepared’ (4), with a total score ranging from 0 to 32.single items covering the intervention topics: a) medical issues including symptoms and symptom relief; b) communication within the couple, how to spend the time before death, being family member and caregiver, planning for the moment of death; and c) considerations of the family caregiver’s future, including psychological issues, logistical issues, finances, and the care of children.single items about psychological health and quality of life

Feasibility will be evaluated through semi-structured interviews (aim I). Preparedness for caregiving will be measured at baseline and 4 weeks later (aim II). Preparedness for death and associations with preparedness for caregiving will be measured 8 weeks after the patient’s death (aim II). Intervention topics will be measured at baseline and 4 weeks later (aim III). Family caregivers’ physical and psychological health and quality of life will be measured 1 year later (aim IV).

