## Background

Although there are great variations, family caregivers of patients with severe illness often face numerous tasks involving the practical and medical caregiving for the patient while also providing emotional, social and existential support as well as maintaining household chores [1]. They may or may not recognize themselves as caregivers; nevertheless, the scientific literature defines a family caregiver as any relative, friend, or family caregiver who has a significant relationship with, and provides various forms of assistance to, an ill person. Thus, the term ‘caregiving’ covers a broad perspective [2]. Family caregivers often report being insufficiently prepared for the caregiver role as well as a consequent need for information and psychosocial support [3, 4]. Preparedness for caregiving refers to how ready the family caregivers themselves perceive they are for the tasks related to the caregiving role, such as providing physical care, emotional support and dealing with the stress of caregiving. Thus, preparedness for caregiving has both a practical and emotional component; knowing what to do, but also coping with emotions and stress [5]. Feelings of being prepared are associated with several positive aspects, such as less burden and anxiety, and can be regarded as a protective factor against negative consequences. Preparedness may also promote stronger feelings of reward and hope as well as better health [6, 7]. Increased feelings of preparedness for family caregivers have been suggested to possibly affect the patient in a favorable way [8].

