### Aims

The overall aim of the research is to examine the use of and potential influences of a web-based intervention targeting family caregivers of patients affected by severe illness who are cared for at home. To reach a deeper understanding for such an approach, the following four specific aims will be addressed:
Specific aim I: To evaluate feasibility in terms of framework, content, usage and family caregivers’ experiences of a web-based psycho-educational intervention. *Family caregivers will be interviewed and statistics concerning their use of the website will be used.*Specific aim II: To explore how the use of a website influences family caregivers’ degree of preparedness for caregiving and death. *Preparedness for caregiving will be measured at baseline and 4 weeks later. Preparedness for death and associations with preparedness for caregiving will be measured 8 weeks after the patient’s death. Interviews will also be used for data collection.*Specific aim III: To explore how the use of a website influences family caregivers’ knowledge about medical issues, their communication with the patient, and their considerations of the future. *Measurements will be performed at baseline and 4 weeks later. Interviews will also be used for data collection.*Specific aim IV: To investigate how family caregivers’ degree of preparedness for caregiving and death influences their physical and psychological health and quality of life 1 year after the patient’s death. *Information collected as described for the specific aims II and III will be related to physical and psychological health, measured 1 year after the patient’s death.*

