#### Statistical analysis

In the analysis of preparedness for caregiving (aim II), we will address the statistical null hypothesis by analyzing mean differences between two dependent means (pre- and post-intervention). Cut-off values for low, moderate and high preparedness have been established through earlier studies [24] and will be applied to the results. Preparedness for death (aim II) will be examined using descriptive statistics, and associations with preparedness for caregiving will be investigated with the use of linear regression analysis. Guided by the intention-to-intervene (intervention to treat) principle, we will include all family caregivers for whom we have information on the respective outcome. For aims III and IV we will proceed in a similar manner.

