#### Statistical power

Statistical power was calculated based on the preparedness for caregiving scale [5, 46]. As a model, we used a previous intervention study [24], where a statistically significant (alpha = 0.05) improvement in preparedness for caregiving was observed between two dependent means (*t*-tests) with an effect size of 0.27. In order to obtain statistical power of 80%, we would need 109 participants. However, with regard to the number of attritions in the previous intervention study, we decided to raise the required sample to 200 participants.

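### Aim IV asks how preparedness influences health one year after the death, but health is timed only at one year, so prior health could account for part or all of the association

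*Protocol article*

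**What the plan says.** The protocol article's Aims section states aim IV as how caregivers' "degree of preparedness for caregiving and death influences their physical and psychological health and quality of life 1 year after the patient" has died. The note to that aim says that the information collected for aims II and III, meaning preparedness and the intervention topics, will be related to health at one year.

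Data collection and measures gives the timing of each construct:
- preparedness for caregiving and the topics: baseline and 4 weeks;
- preparedness for death: 8 weeks after the death;
- health: "physical and psychological health and quality of life will be measured 1 year later (aim IV").

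The questionnaire contents in the same section include "single items about psychological health and quality of life", with no time-point attached. The Abstract says that the questionnaire is given on four occasions.

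Statistical analysis describes a paired comparison of means, descriptive statistics and linear regression for aim II, then says: "For aims III and IV we will proceed in a similar manner". It names no covariate for aim IV.

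The Background says: "Feelings of being prepared are associated with several positive aspects, such as less burden and anxiety". It also cites studies in which reducing caregivers' distress before the loss, among other things, may improve adjustment afterwards.

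**The concern.** There is no control group, so aim IV is an observational comparison of better- and less-prepared caregivers. A caregiver who is anxious or low at enrolment may rate preparedness as poor and may also be in poor health a year after the death, without preparedness having changed anything. With no earlier health value in the model, the coefficient mixes that prior state with any benefit of preparedness.

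Preparedness for death has a further problem. It is rated 8 weeks after the death, so grief at that moment can affect the rating as well as the later outcome.

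The Abstract and Discussion suggest that factors identified before death, and their association with long-term health, may change clinical work. A coefficient read as influence could be used to justify support aimed at preparedness when the driver is prior health. An analysis plan can add covariates, but it cannot add a value that was never collected. The measurement schedule is therefore the decisive point.

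**Working it through.** **The plan's own figure.** Statistical power relies on an earlier study in which "a statistically significant (alpha = 0.05) improvement in preparedness for caregiving was observed between two dependent means" "with an effect size of 0.27", and says: "In order to obtain statistical power of 80%, we would need 109 participants". With two-sided alpha 0.05:
- normal approximation: n = ((1.960 + 0.842)/0.27)² = 107.7, so 108;
- exact paired t-test: 110, with power 79.8% at 109.

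The stated figure is reproduced to within 2. It concerns aim II and says nothing about aim IV. I use 109 below only as a benchmark number of respondents.

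**Which aim II method carries over.** A paired comparison needs two measurements of the outcome, and health is timed once. Descriptive statistics do not address influence. Linear regression of one-year health on preparedness is the method that fits. This is an inference from the cross-reference and is not stated outright.

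**Confounding with no true effect.** Let prior health H correlate *a* with preparedness and *b* with one-year health, and let preparedness have no effect. The spurious correlation is r = a × b. The chance of p < 0.05 by Fisher's z is Φ(q − 1.96) + Φ(−q − 1.96), where q = atanh(r) × √(n − 3). The documents give neither *a* nor *b*, nor the number with one-year data, so all three are assumptions shown over a range.

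| a × b | r | n = 60 | n = 109 | n = 200 |
|---|---|---|---|---|
| 0.2 × 0.4 | 0.08 | 9% | 13% | 20% |
| 0.3 × 0.5 | 0.15 | 21% | 34% | 56% |
| 0.4 × 0.6 | 0.24 | 46% | 71% | 93% |
| 0.5 × 0.6 | 0.30 | 65% | 89% | 99% |

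Example for n = 109 and r = 0.15: q = 0.151 × √106 = 1.556. Φ(−0.404) is about 0.343, and the other tail is negligible.

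**What adjustment achieves.** Least-squares regressions were simulated (2,000 runs per scenario), again with no true effect. The last column uses a baseline measure of reliability 0.6, also an assumption.

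| a, b | n | Slope, significant: no earlier health | Significant: H without error | Slope, significant: H with reliability 0.6 |
|---|---|---|---|---|
| 0.3, 0.5 | 109 | 0.15, 35% | 5% | 0.06, 11% |
| 0.4, 0.6 | 109 | 0.24, 73% | 5% | 0.11, 20% |
| 0.3, 0.5 | 200 | 0.15, 58% | 4% | 0.06, 16% |
| 0.4, 0.6 | 200 | 0.24, 93% | 4% | 0.11, 36% |

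The residual slope agrees with the formula ab(1 − ρ)/(1 − a²ρ), where ρ is the reliability: 0.15 × 0.4/0.946 = 0.063 and 0.24 × 0.4/0.904 = 0.106. An imperfect baseline measure removes more than half of the bias but not all of it. None of this addresses grief at the time of the 8-week rating.

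**The case against.** A reader might infer that no earlier health value is collected at all. The documents do not establish that. The psychological-health and quality-of-life items are listed without time-points in a questionnaire given four times, the first at baseline, and the research flow chart is not shown. The items may already be asked at baseline. What stands is that the only timing given for health is one year, and that the description of aim IV draws on no earlier health value.

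A reader might also infer that prior health explains the whole association. That is only a possibility. The Background reports an association and calls preparedness protective, which points from preparedness to health. It makes confounding plausible but does not show a common cause. With weak links the spurious correlation is only 0.08.

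A third inference would be that physical health has no measure, because the item list omits it. The list is visibly incomplete: preparedness for death has no entry of its own either, yet it is scheduled. Three sections say that physical health is an outcome. I do not press this.

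Covariate lists are normally left to an analysis plan, and the sentence carrying over the aim II methods does not exclude adjustment. That is fair for age, gender and education, which are collected. It is no answer for baseline health if baseline health is not asked.

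Finally, one-year health is one of several secondary outcomes in a study described as a first step, and parts of the text already speak of association. This lowers the stakes, but aim IV is still framed as influence.

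**Conclusion.** The point holds for the schedule and analysis as written. Health is timed only at one year, aim IV uses no earlier health value, and its wording is causal. Prior health could therefore produce part or all of the association. How much is unknown. If the links are 0.2 × 0.4 to 0.5 × 0.6, the spurious correlation is 0.08 to 0.30, significant in about 13% to 89% of analyses with 109 respondents and no true effect. Those correlations and the number of one-year respondents are assumptions. The conclusion also rests on reading regression as the method carried over. If the health items are already in the baseline questionnaire, only the analysis and the wording need to change.

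The preparedness-for-death rating is the weaker exposure of the two, because it is taken after the loss and baseline health cannot remove the effect of current grief on it. This merits correction, but it concerns a secondary aim and does not affect the pre-post comparison in aim II.

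**What to change.** 1. State when the psychological-health and quality-of-life items are asked. If they are not in the baseline electronic questionnaire, add them, with whatever physical-health item is used at one year. If they are already there, use them.
2. Regress each one-year outcome on the 4-week preparedness for caregiving score, adjusting for the baseline value of that outcome, age, gender and education.
3. Report the 8-week preparedness-for-death rating in a separate analysis, labelled as a retrospective association.
4. In aim IV, replace *influences* with *is associated with*. Adjustment for single items leaves residual confounding, so the softer wording is needed even after steps 1 and 2.

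The cost is a slightly longer baseline form and some rewording. There is one statistical price: if preparedness at enrolment has already affected health, adjusting for baseline health removes that part of the effect. The write-up should say so. If the items are not yet asked at baseline, the value cannot be recovered for caregivers who have already passed that point, so the change is worth making early.

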### Data analyses

#### Analysis of interviews

For aim I, data from the semi-structured interviews with participants will be analyzed through qualitative content analysis [47].

#### Statistical analysis

In the analysis of preparedness for caregiving (aim II), we will address the statistical null hypothesis by analyzing mean differences between two dependent means (pre- and post-intervention). Cut-off values for low, moderate and high preparedness have been established through earlier studies [24] and will be applied to the results. Preparedness for death (aim II) will be examined using descriptive statistics, and associations with preparedness for caregiving will be investigated with the use of linear regression analysis. Guided by the intention-to-intervene (intervention to treat) principle, we will include all family caregivers for whom we have information on the respective outcome. For aims III and IV we will proceed in a similar manner.

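### The analysis labelled intention-to-intervene is an available-case rule, so the pre-post change describes caregivers who returned both questionnaires, not all who completed baseline

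*Protocol article*

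**What the plan says.** The Statistical analysis section of the protocol article sets the population in one sentence: "Guided by the intention-to-intervene (intervention to treat) principle, we will include all family caregivers for whom we have information on the respective outcome". For preparedness for caregiving (aim II), the same section tests the null hypothesis by "analyzing mean differences between two dependent means (pre- and post-intervention"). It carries the approach over to aims III and IV.

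The two measurements are fixed under Data collection and measures: "Preparedness for caregiving will be measured at baseline and 4 weeks later (aim II"). Under Statistical power, 109 participants are needed, and then "with regard to the number of attritions in the previous intervention study, we decided to raise the required sample to 200 participants". The Inclusion criteria section gives the same reason for the figure of 200.

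The Outcomes section adds that website use is logged: "Information about which participants have logged on to narstaende.se, which videos have been watched and how many times a specific video was watched can be" collected electronically. It says that use can be studied in relation to preparedness.

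**The concern.** The label and the rule in that sentence do not agree. An intention-to-treat type of principle has two parts: participants stay in the analysis whatever intervention they took up, and everyone enrolled is included. The stated rule meets the first part and fails the second. A paired difference needs both scores, so a caregiver without the 4-week score contributes no change.

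This matters because loss is unlikely to be random here. The patients have a prognosis of months, and the Ethical considerations section calls the caregivers particularly vulnerable. A patient's decline or death, or the caregiver's own strain, could stop the 4-week questionnaire coming back, and each may be related to preparedness. The design has one group, so no control arm with similar loss is available for comparison, and the completers' change is the whole result. Recruiting 200 instead of 109 protects precision but does not remove bias from selective loss. A reader who sees the label may think attrition has been dealt with when it has not.

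**Working it through.** **Inputs from the Statistical power section.** Alpha 0.05 (sidedness not stated), power 80%, effect size 0.27, 109 needed, 200 recruited. I take 0.27 as the mean paired change divided by the SD of the change. The SD units below have that meaning.

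**Reproducing 109.** Two-sided normal approximation: n = ((1.960 + 0.842)/0.27)² = 107.7, so 108. The exact noncentral t calculation gives 110 (power 0.801), and power at 109 is 0.798. The stated 109 is therefore reproduced as the number of complete pairs for a two-sided test. One-sided versions give 85 (normal) or 87 (t) and do not reproduce it.

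**Attrition allowance.** 1 − 109/200 = 91/200 = 45.5%. This is the loss at which the calculated number is still met. It is not a stated rate.

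**What loss can do to the estimate.** Let *a* be the proportion with a baseline score but no 4-week score, and *x* the mean change among them in SD units. If completers change by 0.27 SD:

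change in all with a baseline score = (1 − *a*) × 0.27 + *a* × *x*

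Both *a* and *x* are assumptions. The value 45.5% is the allowance above; 20% is a milder case chosen for illustration.

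| Change among those lost, *x* | *a* = 45.5% | *a* = 20% |
|---|---|---|
| +0.27 (same as completers) | 0.147 + 0.123 = 0.27 | 0.216 + 0.054 = 0.27 |
| 0 | 0.545 × 0.27 = 0.147 | 0.80 × 0.27 = 0.216 |
| −0.27 | 0.147 − 0.123 = 0.024 | 0.216 − 0.054 = 0.162 |

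At 45.5% loss the change in all with a baseline score reaches zero when *x* = −0.147/0.455 = −0.32 SD. If *x* is above 0.27, the formula gives more than 0.27, and the completer analysis then understates the change. In every row the completer estimate is 0.27, so the planned analysis cannot tell these situations apart.

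The calculation treats every lost caregiver as having a definable 4-week change. Those bereaved before 4 weeks do not have one, so they belong outside *a*.

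**The case against.** The best defence is that the text is open about its rule. It says the analysis is guided by a principle and states in the same sentence who is included. With one group there is no randomised comparison to preserve, and the part of the principle that can apply, keeping caregivers regardless of website use, is respected. The study also presents itself as exploratory, and missing-data models are commonly left to a full protocol or analysis plan that is not shown. Much of this stands: the absence of an imputation section is no finding. What remains is that the article itself fixes a label and a population that do not match, for the outcome on which the power calculation rests.

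A reader might infer stronger things that the documents do not support:

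- **That a 45% loss is planned at 4 weeks.** No rate is given, and data are collected at four time-points, the last 1 year after the patient's death. The 45.5% is a tolerance.
- **That the completer result is too large by a known factor, such as 0.27/0.147 = 1.83.** That requires the whole 45.5% to be lost by week 4 and no change among those lost. Larger gains among them would reverse the bias.
- **That data from those lost are discarded.** The Aims section uses website statistics for feasibility, and the Outcomes section relates use to preparedness. Those lost only drop out of the paired change.
- **That the target should be everyone offered the website.** Caregivers who never register or complete baseline have no data for any model. The reachable target is all who completed baseline.

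It is also fair to say that a mixed model or multiple imputation assumes data are missing at random, which cannot be verified. The suggested auxiliary variables do not measure strain or patient condition directly. That is why a sensitivity analysis is needed as well.

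**Conclusion.** The concern holds in a limited form. The rule is available-case, it is labelled as something broader, and for the paired test it means completers of both questionnaires. The protocol expects attrition, and there are plausible reasons for it to be related to preparedness. The completers' change may therefore differ from the change among all who completed baseline.

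The document does not allow the size or direction of that difference to be determined. The tabulated figures show only how far the two quantities could part under assumed losses and assumed changes among those lost. They rest on reading 0.27 as a standardised paired change and on completers achieving exactly that value.

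**What to change.** 1. Call the stated rule available-case, and say that caregivers are kept regardless of website use.
2. Estimate the pre-post change with a likelihood-based repeated-measures model, or multiple imputation, that uses every caregiver with a baseline score. Use baseline preparedness, age, gender, education and logged website use as auxiliary variables. Report the completer paired t-test beside it.
3. Add a delta-type sensitivity analysis over a range of assumed changes for non-responders whose patient was alive at 4 weeks.
4. Report caregivers bereaved before 4 weeks separately, without imputing a caregiving score for them.
5. Compare the baseline data of completers with those of caregivers lost.

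The cost is a wording change and a little programming. The baseline variables and website logs are already to be collected; patient status at 4 weeks must be known for steps 3 and 4. The downsides are the model's reliance on missing-at-random and an estimate that may be less favourable. The change should be made before results are seen.
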